### Intervention

Trained physicians will perform lung ultrasound following the Bedside Lung Ultrasound in Emergency (BLUE) protocol technique [34]—an ultrasound protocol to identify points at the thoracic cage of patients using both hands of the investigator (Figure 2)—to identify pulmonary edema by the appearance of B lines [26].

Panel A shows a patient with sepsis admitted to the emergency department. Patient will be surveyed for eligibility and will accordingly receive either fluid limited by lung ultrasound or 30 mL/kg (ie, the control group). Ultrasound will be performed as per the BLUE protocol. Panel B shows how to identify points on the thoracic cage of a patient through morphological examination using both hands: little finger of the upper hand is just below the clavicle, fingertips at middle line, and the lower hand below the upper hand. The upper BLUE-point is at the middle of the upper hand, and the lower BLUE-point is at the middle of the lower palm, creating 4 points in both hemithoraxes. At these points (1-4, as shown in panel C), ultrasound will be conducted and fluid will be given until 3 B lines appear in the ultrasound. BLUE protocol defines B lines as those vertical and echogenic narrow-based lines that widen progressively as they pass to the other end of the image [25,34].

A phased array (1-5 MHz) transducer will be used. The images will be acquired while the patient is in a supine position, saved, and coded for further quality control and assessing inter-rater reliability. A baseline lung-ultrasound scan to assess the extent of B lines (Figure 2) will be performed. Subsequently, the resuscitation target in the intervention arm will be determined or limited by lung ultrasound as follows (Figure 1). Repeated ultrasound scan will be performed after the initial 15 mL/kg IV fluid bolus in the intervention arm and then after every 500 mL of fluid administration. If 2 B lines appear, scans will be performed after every additional 300 mL of fluid in the intervention arm. When 3 or more B lines are present bilaterally in more than 2 areas, further fluid administration will be stopped. Therefore, fluid resuscitation target for the intervention group is to administer volume until the appearance of 3 B lines (Figure1). If a further hemodynamic compromise is detected in the intervention arm following IV fluid discontinuation, vasopressors will be started or continued as per the Sepsis-3 guidelines (Figure 1).

The control arm will be assessed by a baseline lung ultrasound to document the absence of B lines and will then receive at least 30 mL/kg fluids as per the Sepsis-3 guidelines. After the initial bolus, the type and rate of IV fluid administration will be left to the discretion of the treating physician and the local emergency departments’ protocols. All concomitant care and interventions are permitted during the trial.

**Figure 2 figure2:**
[figure not shown]
Bedside Lung Ultrasound in Emergency (BLUE) protocol.

### Outcomes

The primary outcome is the oxygenation (measured as mean PaO_2_/FiO_2_) at 48 hours after IV fluid administration. We expect a higher mean of PaO_2_/FiO_2_ in the intervention arm, which will be considered beneficial. A lower PaO_2_/FiO_2_ ratio is a sign of oxygenation compromise, which can occur with excessive fluid administration and increased EVLW. We will use PaO_2_/FiO_2_ ratio because it is a reliable and commonly used index of oxygenation that is easy to obtain and clinically significant as a predictor for mortality in patients with sepsis [26,35]. Arterial blood samples will be obtained for PaO_2_ measurement. FiO_2_ will be estimated based on widely accepted approximated values for those patients not mechanically ventilated [36].

The secondary outcomes will be assessed at time points of 0, 6, 12, 24, and 48 hours and after 15mL/kg of fluid administration, and also at 30 days. We will then evaluate (1) means of PaO_2_/FiO_2_ ratio between groups at these time points, (2) the incidence of pulmonary outcomes (pulmonary edema, acute respiratory distress syndrome, or need for invasive mechanical ventilation), (3) mean SOFA score, (4) mean creatinine level (in milligram per deciliter), (5) mean amount of volume of administered fluid, and (6) proportion frequency of 30-day mortality. Additionally, the type of IV fluid will be documented (Table 1).

Pulmonary outcomes (namely, pulmonary edema) will be confirmed by physicians based on symptoms and signs (eg, shortness of breath after fluid resuscitation and crackles), laboratory parameters (raised NT-proBNP, adjusted for age [37]), and x-ray findings suggestive of pulmonary edema.

The outcomes will be measured and documented in data collection forms by a nurse from the participating center. These forms will be made available in the protocol. Reliability and validity of laboratory tests at different participating centers will be made available in the protocol.

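### Administered fluid volume has no stated unit and is assigned an unadjusted test, although both starting doses are per kilogram; a baseline-weight term would sharpen the comparison at almost no cost

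*Protocol article*

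**What the plan says.** All references are to the Methods of the protocol article.

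- **Outcomes.** The fifth secondary outcome is the "mean amount of volume of administered fluid". No unit is attached, whereas creatinine, listed just before it, has one (mg/dL).
- **Statistical Analysis.** Continuous secondary outcomes are to be analysed by repeated-measures ANOVA and t test. No covariate is named.
- **Intervention, control arm.** Patients "will then receive at least 30 mL/kg fluids". After the bolus, "the type and rate of IV fluid administration will be left to the discretion of the treating physician".
- **Intervention, ultrasound arm.** Scans are repeated "after the initial 15 mL/kg IV fluid bolus in the intervention arm and then after every 500 mL of fluid administration". Once two B lines appear, "scans will be performed after every additional 300 mL of fluid in the intervention arm".
- **Randomization and Blinding.** Stratification is by age and center, not by weight.

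**The concern.** Starting doses are set per kilogram, so patients treated identically receive different volumes. At 30 mL/kg a 50-kg patient gets 30 × 50 = 1500 mL and a 100-kg patient gets 30 × 100 = 3000 mL. If volume is compared in millilitres without weight in the model, that spread goes into the error term, although a baseline value needed for dosing could remove much of it.

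This outcome has a particular job. Repeat scans are specified only for the ultrasound arm, and fluid type is merely documented, so volume is in effect the only listed quantity that shows how far the arms' fluid treatment diverged. If the PaO2/FiO2 result is null, readers will look at volume to judge whether the strategy failed or the arms were treated much alike. A wider interval than necessary makes that harder to judge.

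**Working it through.** **1. The plan's own figure.** The article states no figure for the volume comparison. Its sample size is for the primary outcome: difference 25 mm Hg, SDs 81 and 78 (about 80), alpha 0.05 (two-sided assumed), power 0.80.

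n per arm = 2 × (1.960 + 0.842)² × 80² / 25² ≈ 161, and 161 / 0.95 ≈ 170.

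The stated 170 per arm is reproduced. This point does not affect it. I use 161 evaluable patients per arm below.

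**2. Variance with and without a weight term.** The documents give no weight distribution or volume SD, so the inputs are assumptions: mean dose μ = 30 mL/kg; between-patient SD s = 10 to 15 mL/kg; weight with mean m and coefficient of variation c = 0.15 to 0.25; dose per kg independent of weight; volume fully proportional to weight.

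- Unadjusted variance in mL: m² × [s²(1 + c²) + μ²c²]
- Residual variance after a linear weight term: m² × s²(1 + c²)
- Ratio: 1 + μ²c² / [s²(1 + c²)]
- Share of variance removed: 1 − 1/ratio

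| s (mL/kg) | c | Ratio | Variance removed |
|---|---|---|---|
| 15 | 0.15 | 1 + 4 × 0.0225/1.0225 = 1.09 | 8% |
| 15 | 0.20 | 1 + 4 × 0.04/1.04 = 1.15 | 13% |
| 10 | 0.20 | 1 + 9 × 0.04/1.04 = 1.35 | 26% |
| 10 | 0.25 | 1 + 9 × 0.0625/1.0625 = 1.53 | 35% |

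A confidence interval narrows by 1 − 1/√ratio, which is about 4% to 19%. For scale, take m = 75 kg, s = 10 and c = 0.20. The SD is 75 × √140 ≈ 887 mL unadjusted and 75 × √104 ≈ 765 mL adjusted. With 161 per arm the 95% half-width is 1.96 × SD × √(2/161), about 194 mL against 167 mL.

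**3. Relaxing proportionality.** A simulation treated the per-kg starting doses as minimum doses and let further fluid be either per kg or in absolute mL. At weight 75 kg (SD 15), fluid SD 10 mL/kg and nominal means of 35 v 30 mL/kg:

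- further fluid per kg: SD 821 unadjusted, 652 adjusted; variance ratio (821/652)² ≈ 1.59
- further fluid in absolute mL: SD 730 unadjusted, 648 adjusted; variance ratio (730/648)² ≈ 1.27

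The closed form gives 1.35 for the same c and s, so the real gain could lie on either side of it.

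**4. Consequence for power at 161 per arm.** Ranges are over weight 70 kg (SD 12) to 80 kg (SD 20) and fluid SD 5 to 15 mL/kg.

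| Nominal means, control v ultrasound (mL/kg) | Unadjusted | Weight-adjusted |
|---|---|---|
| 33 v 25 | >0.999 | >0.999 |
| 35 v 30 | 0.996 to >0.999 | >0.999 |
| 33 v 31 | 0.79 to 0.99 | 0.985 to >0.999 |

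**5. Covariate or mL/kg?** At weight 75 kg (SD 15), fluid SD 15 mL/kg, 35 v 30 mL/kg and further fluid in absolute mL, the standardised difference was 0.61 for unadjusted mL, 0.56 for mL/kg and 0.64 for mL with weight as covariate. Dividing by weight can therefore lose efficiency when part of the fluid is not dosed by weight; the covariate form did not.

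**The case against.** The strongest case against is that this is an efficiency preference for one secondary outcome in a condensed article, and that scale and covariates are ordinarily left to the full protocol or analysis plan. That is fair as to severity. It does not remove the point, because the article names both the outcome and the test, and the named test makes no use of weight.

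Several stronger readings are tempting, and the documents do not support them:

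- **That the plan commits to raw millilitres.** A reader might infer this from the unscaled wording, but no unit is given and mL/kg is not excluded. The firm defect is the unstated scale.
- **That the comparison is biased, or that a chance weight imbalance invalidates it.** Randomisation keeps the unadjusted difference unbiased. With an assumed weight SD of 15 kg, the standard error of the arm difference in weight is 15 × √(2/161) ≈ 1.7 kg. A 3-kg imbalance is about 1.8 standard errors and moves volume by about 3 × 30 = 90 mL, against 5 × 75 = 375 mL for a 5 mL/kg contrast. The t test's standard error already allows for such imbalances.
- **That volume simply scales with weight.** Only the starting doses do. Later fluid is in 500 mL or 300 mL steps, or at the physician's discretion.
- **That the gain is larger.** Comparing raw variance with (m × s)² gives ratios of 1.11 to 1.63, but a linear weight term does not reach that benchmark. Its own range is 1.09 to 1.53.
- **That volume should not be listed as an outcome.** That is a labelling preference, and nothing here depends on it.

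**Conclusion.** The point holds as a minor one. The scale of the volume outcome is not stated, and the test assigned to it ignores a baseline variable that the dosing itself requires. The cost is precision, not validity. Under the assumed values and full proportionality, a linear weight term removes about 8% to 35% of the variance; the real figure may differ because later fluid is not weight-based. A separation of 5 mL/kg or more would be detected either way (power at least 0.99 in the simulated range). The adjustment makes a visible difference only when the arms end close together: at nominal 33 v 31 mL/kg, unadjusted power falls as low as 0.79 when weight is very variable. Neither the sample size nor the primary analysis is affected.

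**What to change.** In Outcomes, state the unit of the volume outcome. In Statistical Analysis, specify that cumulative volume in mL, at the assessment times already listed, is compared with a linear model containing arm and baseline body weight. Report mL/kg by arm alongside as description, not as the main comparison.

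The cost is a change of wording. No new data are needed, since weight is required for dosing. The Results section says that funding and ethical approval are still being acquired and that the protocol is yet to be registered, so the change can be made before enrollment.

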### Ethical Considerations

The protocol, templates, consent forms, and other requested documents (local language and English versions) will be reviewed and approved by the institutional review board/ethical committee at each participating site for the scientific content and regulatory compliance. Any modifications to the protocol will require a formal amendment and approval by the concerned institutional review board/ethical committee, notification to other research centers, and information update of trial registration [31].

Research investigators and physicians will have an informed discussion about the study details with conscious patients and provide printed information. The study investigator will use clinical judgment to discern between patients competent and incompetent to make a decision regarding their participation. Research investigators will obtain written consent from patients willing to participate in the study and will take the responsibility to protect those patients and follow ethical standards. Since it is likely that these patients might be ill or incompetent of taking decision at the time of giving consent. In such a case, the patient and their legal representative will receive an explanation about study details. They will be asked to provide an informed consent after expressing an understanding of the study procedures. When the patient is incapable of making a decision and there is no legal representative, the patient’s next of kin will be asked (either in-person or by phone) to provide a no-objection form based on his or her understanding of the patient’s wishes. If a no-objection form is provided, the patient will be included in the trial procedure since the intervention and assessment do not involve additional invasive or risky procedures. These patients will be retrospectively consented for their data to be included in the study as is the practice in other protocols [38]. Without a consent/no-objection form, the patient will be excluded from our study and will receive the usual care. We will reconsider the informed consent procedure repeatedly during the study in order to respect patients’ rights to withdraw from the study at any time. Strict data monitoring guidelines will be followed (Multimedia Appendix 4 Data Monitoring).

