**Enrollment**										
	Eligibility screening	X								
	Informed consent	X								
	Registration form	X								
	Baseline assessment (clinical features): sepsis with a qSOFA^b^ score≥2; low systolic blood pressure≤100 mmHg; respiratory rate≥22 breaths per minute; altered mentation with Glasgow coma scale score<15		X							
	Baseline assessment (laboratory parameters): ultrasound; PaO_2_/FiO_2_; arterial blood gas analysis; x-ray, NT-proBNP		X							
	Allocation		X							

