**Assessments**										
	Primary (PaO_2_/FiO_2_)^c^		X	X	X	X	X			
	Secondary: PaO_2_/FiO_2_/Pulmonary outcome/SOFA^d^ score/creatinine/volume		X	X	X	X	X			
	Prognosis (30-day mortality)								X	
	Documentation (amount of fluid)			X	X	X	X	X		

^a^T1: timepoint 1 before baseline; unknown units of time.

^b^qSOFA: quick Sequential Organ Failure Assessment.

^c^PaO_2_/FiO_2_: partial pressure of arterial oxygen/ fraction of inspired oxygen.

^d^SOFA: Sequential Organ Failure Assessment.

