### Eligibility Criteria

The eligibility criteria for patient recruitment is shown in Textbox 1.

Inclusion and exclusion criteria for patient recruitment.Inclusion Criteria:Admitted into the emergency department.Age 18-65 years.Sepsis with a quick Sequential Organ Failure Assessment (qSOFA) score≥2 [3,14,28,33]Consent by the patient or legal guardian.Exclusion Criteria:Mechanical ventilation at screening.Unconsciousness when admitted to emergency department (with Glasgow Coma Scale score<8)Preexisting pulmonary pathology as assessed by clinical symptoms or radiographic evidence in chest x-ray or by pulmonary bedside ultrasound (>2 B lines, a comet-tail artifact)History of pulmonary disorders (chronic obstructive pulmonary disease, asthma, parenchymal lung disease, or edema) or procedures.Preexisting cardiac pathology, disease, or dysfunction (ejection fraction<50, New York Health Association class>2) lung, or cardiac surgical procedures.History of liver cirrhosis, cancer, autoimmune disease, or immunosuppression.Patients under palliative care and patients facing imminent and inevitable death in the next 30 days due to causes other than sepsisSevere burns.Advanced kidney disease (chronic kidney disease stage 4 or above)Unstable medical conditions (eg, uncontrolled diabetes, uncompensated cardiac issues, heart failure, or chronic obstructive pulmonary disease).PregnancyWith other reasons or diseases needing a restricted fluid administration

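### The no-objection route for incapacitated patients rests on the absence of additional invasive or risky procedures, but the schedule sets five, possibly six, arterial samples in 48 hours and nothing says these are usual care

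*Protocol article*

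**What the plan says.** **Ethical Considerations.** If a patient cannot decide and has no legal representative, the "next of kin will be asked (either in-person or by phone) to provide a no-objection form". With that form the patient enters the trial, and the reason given is "since the intervention and assessment do not involve additional invasive or risky procedures". Consent for use of the data is sought afterwards.

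**Outcomes.** "Arterial blood samples will be obtained for PaO_2_ measurement". On timing: "The secondary outcomes will be assessed at time points of 0, 6, 12, 24, and 48 hours and after 15mL/kg of fluid administration". The first secondary outcome is the "means of PaO_2_/FiO_2_ ratio between groups at these time points".

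**Table 1.** The assessment row "Primary (PaO_2_/FiO_2_)^c" is marked at 0, 6, 12, 24 and 48 h. No column exists for an assessment after 15 mL/kg. The baseline row at 0 h includes "arterial blood gas analysis; x-ray, NT-proBNP".

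**Randomization and Blinding.** Drawing blood for PaO2/FiO2 is listed among the tasks of the blinded study investigators, as distinct from the treating physician.

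**Textbox 1.** The first exclusion is "Mechanical ventilation at screening".

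**Intervention.** In the ultrasound arm, fluid is stopped when the B-line criterion is met. The control arm receives at least 30 mL/kg.

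**The concern.** The statement about procedures is the stated reason for enrolling patients who cannot consent and have no legal representative. If the rest of the protocol does not bear it out, that enrolment condition rests on a property the design has not been shown to have.

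These patients are not a remote possibility. Altered mentation is one of the qSOFA features listed at baseline, only a Glasgow Coma Scale score below 8 is excluded, and Ethical Considerations itself expects that patients may be unable to decide. The later consent concerns use of the data. By then some or all of the sampling and the allocated fluid strategy may already have taken place.

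What is at stake is whether burden and risk are described accurately to review boards and relatives. No estimate, error rate or sample size depends on it.

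**Working it through.** The protocol gives no total for arterial samples, so there is no figure to reproduce. The check is a count, followed by a comparison of sections.

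**1. Is the assessment invasive?** PaO2 requires arterial blood (Outcomes), so each scheduled PaO2/FiO2 value requires an arterial sample.

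**2. How many are scheduled?**
- Table 1: 0, 6, 12, 24 and 48 h = 5 occasions. The baseline blood gas at 0 h is the same occasion as the baseline PaO2/FiO2 and is not counted twice.
- Outcomes: the same five plus one after 15 mL/kg = 5 + 1 = 6.
- If the 15 mL/kg point coincides with a clock time, the total returns to 5. The Abstract and Introduction join the 15 mL/kg and the clock times in one phrase, which can also be read as implying no separate sample.

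**3. How many are additional to usual care?** The protocol does not say. Under stated assumptions:

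| Assumption | Table 1 only | Table 1 plus after 15 mL/kg |
|---|---|---|
| None is usual care | 5 | 6 |
| Baseline gas is usual care | 5 − 1 = 4 | 6 − 1 = 5 |
| Further samples are usual care or from a line already in place | fewer than 4 | fewer than 5 |

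The premise about assessment is literally true only if every sample is usual care. The protocol does not claim that.

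**4. Is there text indicating usual care?** I found none for the serial samples. Two features point the other way: study investigators draw the blood, and the times are fixed by the outcome schedule. Patients are not ventilated at screening, and Outcomes provides for estimating FiO2 in patients who are not ventilated, so sampling outside ventilation is expected. How many would have an arterial line is not stated.

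**5. Is the intervention free of added risk on the document's own terms?** Fluid may stop on an ultrasound criterion before the volume given to controls. The Introduction describes prompt and adequate fluid as essential to lowering sepsis mortality and excess fluid as harmful. The Discussion says the guiding ultrasound protocol still lacks good validation. Sample Size Justification plans an interim safety analysis reported to a safety committee. None of this shows that either strategy is the riskier one. It does show that the question is open, which an unqualified statement of no added risk does not convey.

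**The case against.** The best defence turns on the word additional. The sentence denies only procedures beyond usual care. PaO2/FiO2 is a component of SOFA, treating physicians are to follow Sepsis-3, and Outcomes describes the ratio as common and easy to obtain. Some gases would probably be taken anyway. This stands in part: it lowers the number of extra samples and means the sentence cannot be called false for every sample. It does not rescue an unqualified statement, because the protocol nowhere says that five or six samples at fixed times are routine.

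A second defence is that the sentence speaks of procedures, and the procedure added by the intervention is an ultrasound scan. That is a fair reading of one word. But the sentence covers the intervention as a whole, and the intervention determines how much fluid is given.

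A third defence is that there are safeguards: boards review the protocol and forms, consent is revisited during the study, and patients may withdraw. These stand, and they limit the harm.

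Several stronger readings are tempting, and the document does not support them:
- **That boards and relatives are misinformed.** The consent and no-objection forms are not shown, and boards would see the sampling schedule.
- **That the burden is six samples times all 340 patients.** The premise concerns only patients enrolled on a no-objection form, whose number is not stated, and six is an upper bound.
- **That repeated punctures would lead less sick patients to refuse the 48 h sample and bias the primary endpoint.** Nothing in the document bears on this, and it mainly concerns patients able to decide for themselves.
- **That the 6, 12 and 24 h samples should be limited to clinically indicated gases, or the 15 mL/kg value dropped.** Missing values would then depend on severity. The change would also affect stated secondary outcomes, the respiratory part of SOFA and the repeated-measures analysis.

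**Conclusion.** The point holds as an internal contradiction about an enrolment condition. The justification in Ethical Considerations is not supported by Outcomes, Table 1, or Randomization and Blinding. Five arterial samples per patient are scheduled over 48 h, with a possible sixth after 15 mL/kg. The number that is additional is therefore at most five or six, and it falls with each sample shown to be usual care. The wording on risk should also not stand unqualified, because the intervention may give less fluid than the control arm receives.

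The conclusion assumes that each PaO2/FiO2 value needs its own arterial sample and that the article's silence on usual care reflects the plan. A statement that every serial sample is usual care would settle the sampling half, but not the wording on risk. The conclusion takes no position on which fluid strategy is right.

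**What to change.** Before ethics submission:

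1. Reconcile Ethical Considerations with Outcomes, Table 1, and Randomization and Blinding. Either document that the serial arterial samples are usual care at the participating centers, or delete the premise.
2. If the premise is deleted, state in the consent and no-objection forms how many arterial samples are taken for the trial and that the intervention may restrict fluid. Ask the review boards to judge the no-objection route on that description. If the samples are instead shown to be usual care, the wording on risk still needs qualifying in view of the possible fluid restriction.
3. Reconcile the after-15 mL/kg assessment with Table 1: add a column if it is a separate sample, or state in Outcomes that it coincides with a clock time. Word the Abstract and Introduction to match.
4. Keep the sampling schedule otherwise.

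The cost is small: a reworded paragraph, the matching text in two forms, and one clarification of the schedule. No outcome, analysis or sample size changes. According to Results, ethical approval is still being acquired and centers are still being selected, so no approved document would need amending. The one real risk for the sponsor is that a board, given the fuller description, may decline or narrow the no-objection route, which could slow recruitment by an amount the document does not allow one to estimate.
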